## **8.4 Changes to the protocol and informed consent form**

If the protocol or informed consent form (ICF) needs an amendment, the principal research site is required to submit such amendment to the Regulatory Agencies and/or other regulating body in each participating country for approval. Approved protocol or ICF amendments will be provided to the investigators by the principal research site prior to implementing the amendment.

For administrative changes, the principal investigator is responsible for notifying the EC.

## **8.5 Deviations from protocol**

### **8.5.1 Compliance to protocol**

No investigative procedures other than those defined in this clinical investigational plan will be undertaken on the enrolled subjects without the written agreement of the EC and the principal research site. It is the Investigator's responsibility to ensure that there are no deviations from the clinical investigational plan and full compliance with all established procedures of the EC is maintained. The Investigator will not deviate from the clinical investigational plan for any reason except in cases of medical emergencies, when the deviation is necessary to protect the life or physical well-being of the subject.

### **8.5.2 Procedures for recording, reporting, and analysing protocol deviations**

A deviation is an instance(s) of failure to follow, intentionally or unintentionally, the requirements of the protocol. All deviations must be reported to the principal research site. The occurrence of clinical investigational plan deviations will be monitored by the designee of participating research sites and trial monitors. It is the Investigators' responsibility to inform their EC of clinical investigational plan deviations in accordance with their specific EC reporting policies and procedures. In the event that an investigative site does not comply with the Investigator Agreement or clinical investigational plan, the principal research site will notify the investigator of the site's non-compliance.

## **8.6 Audits and inspections**

In the event that an investigator is contacted by a Regulatory Agency in relation to this trial, the investigator will notify the site immediately. The investigator and study site research personnel must be available to respond to reasonable requests and inspection queries made during the inspection process. The investigator must provide the principal research site with copies of all correspondence that may affect the review of this trial. The principal research site will provide any needed assistance in response to regulatory inspections. For revision about management and safety of subject, it is the principal investigator's responsibility to obtain the approved protocol or ICF amendments from EC.

The EC's approval of the study protocol or ICF amendment above shall be written documented before implementation.

## **9. STUDY MANAGEMENT**

### **9.1 Training**

#### **9.1.1 Training of Monitors**

The monitors or designee will be trained to the protocol, randomization instructions, electronic case report forms, and study drug usage. The principal research site is responsible for the training.

#### **9.1.2 Training of study site research personnel**

Participating investigators and study site research personnel will be trained during site initiation visits collectively conducted by the representatives designed by The General

Hospital of Northern Theatre Command, the Department of Gastroenterology of Changhai Hospital and the ANKON Medical Technologies (Shanghai, China). All training must be documented and must include or reference the revision of materials used for training, who was trained, the trainer and date of training. Original training records should be maintained at the site in the Regulatory Binder and copies should be dispensed to the principal research site.

Site initiation/training involves a didactic session whereby the protocol, including screening procedures, clinical follow-up procedures, and study drug procedures are reviewed in detail along with investigator responsibilities.

## **9.2 Monitoring of the study**

The trial monitors will monitor the trial over its duration according to the prespecified monitoring plan. The trial monitor will contact each site at appropriate intervals to review investigational data for accuracy and completeness and ensure compliance with the clinical investigation plan. The trial monitor may request all documents and required records that are maintained by the Investigator/Site, including medical records (office, clinic, or hospital) for the subjects in this trial. Source documentation must be available to substantiate proper informed consent procedures, adherence to protocol procedures, adequate reporting and follow-up of adverse events, accuracy of data collected on case report forms, and study drug information. The Investigator and/or study site research personnel will be available for monitoring contact. If a site visit is required, it is expected that the Investigator/Site will provide the trial monitor with a suitable working environment for review of study-related documents.

### **Source data**

The investigator is responsible for maintaining complete and accurate documentation of the trial including but not limited to medical records, trial progress records, laboratory results, case report forms, signed informed consent forms, study drug accountability records, correspondence with the EC, the trial monitors, and the principal research site, as well as adverse event reports and information regarding subject discontinuations.

The investigator is required to maintain information in the subject's medical records which documents and corroborates data entered in the case report forms. The investigator and the associated institution will permit direct access to source data and documents for study-related monitoring, audits, EC review, and regulatory inspections.

Subjects providing informed consent agree to allow the monitor or designee access and copying rights to pertinent information in their medical records concerning their participation in this trial. The investigator will obtain, as part of the informed consent, permission for trial monitors or regulatory authorities to review, in confidence, any

records identifying the subjects in this trial. This information may be shared with regulatory agencies; however, the monitor undertakes not to otherwise release the patient's personal and private information.

### **9.3 Study timetable and end of study**

The trial is estimated to commence May 2017. The last subject follow-up at 12 months post-procedure is expected to occur in May 2019. The total expected duration of the trial is 24 months.

## **10. DATA MANAGEMENT**

A computerized data entry and management system will be developed by Taimei Medical Randomization and Drug Management System. A closed and password protected data entry system has been designed to ensure that only the responsible data entry person and the Data Management site supervisor can enter and/or edit data and this can be done only by using the programs and/or utilities available on the menu system. An audit trail will be created by date/time and user stamping. Range checks, review screens, and various error trapping routines are built into the system as quality control procedures. All possible relevant information on the forms is pre-coded. The statistical analysis of data on this study will be completed by an independent statistical organization, Shenyang Yu Kang Pharmaceutical Technology Co., Ltd.

## **11. EVALUATION AND CALCULATION OF VARIABLES**

### **11.1 Primary Endpoint**

The primary endpoint of this study is the gastric and small intestinal mucosal injury (a composite of erosion, ulceration or bleeding) occurring within 12 months after enrollment.

Situations below can be regarded as valid primary endpoint results, including:

- Successful completion of the AMCE examination at 6 months after randomization (i.e., 12 months after enrollment), regardless of the results of examination;
- AMCE or gastroscopy examination driven by the occurrence of gastrointestinal bleeding at any time during the whole study period observes

new-onset gastric or small intestinal mucosal lesions.

## **11.2 Secondary Endpoint**

1. The incidence and severity of gastric and intestinal mucosal lesions during the first 6 months after study enrollment (prior to randomization);
2. The incidence and severity of gastric and intestinal mucosal lesions after randomization (i.e., between 6 months and 12 months after study enrollment);
3. The incidence of clinically evident gastrointestinal hemorrhage attributed to the upper GI tract (or of unknown origin) during 6 months after study enrollment (prior to randomization);
4. The incidence of clinically evident gastrointestinal hemorrhage attributed to the upper GI tract (or of unknown origin) after randomization (i.e., between 6 months and 12 months after study enrollment);
5. The incidence of clinically evident gastrointestinal hemorrhage attributed to the upper GI tract (or of unknown origin) during 12 months after study enrollment;
6. Gastrointestinal symptoms (pain, nausea/vomiting, dysphagia, other) during the 12 months after enrollment;
7. All bleeding (BARC types 1–5) during the 12 months after enrollment;
8. The incidence of target lesion failure (TLF; cardiac death, target-vessel MI, or clinically-driven target lesion revascularization), during the 12 months after enrollment;
9. The incidence of net adverse clinical events (NACE, defined as TLF or BARC type 2–5 bleeding) during the 12 months after enrollment;
10. The incidence of stent thrombosis (ARC definite, probable, or definite/probable) during the 12 months after enrollment.

## **12. STATISTICAL METHODS AND SAMPLE SIZE**

### **DETERMINATION**

The statistical analyses will be performed using SAS version 9.3.

## **12.1 Description of analysis sets**

The Enrolled Population consists of all subjects who signed informed consent.

The full-analysis-set (FAS) population will consist of all subjects who have been randomized (i.e., when the subject number and allocated treatment are recorded in the EDC database) according to the intention-to-treat (ITT) principle. Subjects will be analyzed in the treatment group assigned by the EDC. The primary endpoint of gastric or intestinal mucosal injury will be analyzed in a modified intention to treat (mITT) population, (i.e., patients with valid primary endpoint results collected).

The per-protocol (PP) population will consist of all randomized subjects without any major deviations from the protocol. The following deviations will lead to exclusion from the PP population:

- Subjects not receiving the assigned treatment as allocated by the EDC or no treatment at all.
- Non-compliance to study drug. Non-compliance is defined as taking less than 80% of dispensed tablets based on manual pill bottle count at each study visit.
- Patients with overdue AMCE or gastroscopy examination at visit 3 (180 days  $\pm$  2 weeks after randomization).

### **12.1.1 Efficacy analysis set**

All efficacy analyses will be performed on the FAS and PP population. The primary efficacy analysis will be performed on the FAS population. This analysis will be repeated in the PP population to support the primary results.

The primary efficacy endpoint gastric or small intestinal mucosal injury occurring within 12 months after enrollment, defined as a composite of erosion, ulceration or bleeding.

### **12.1.2 Safety analysis set**

Safety analyses of study medications will be performed on the FAS population. The safety endpoint is MACCE defined as a composite of cardiac death, target lesion MI, ischemic stroke, clinical-driven TLR or stroke within 12 months after enrollment.

Safety analyses of AMCE examination will be performed in patients undergoing AMCE examination (including GI cleansing). The safety endpoints are digestive symptoms (abdominal distension, nausea, or vomiting, etc.) and retention of capsule endoscopy within 30 days.

## 12.2 Methods of statistical analyses

Continuous variables will be summarised as the number of observations, number of missing values, mean, standard deviation, median, quartiles, and range.

Categorical variables will be summarised as the number of observations, number of missing values, frequencies, and percentages.

Baseline clinical, demographic, laboratory and procedural characteristics will be summarized by randomized treatment group.

Demographic and baseline characteristics will be summarized by randomized treatment group and for all randomized subjects combined (i.e., FAS population). Baseline characteristics that will define subgroups of interest for the efficacy and safety analyses are:

- Age group ( $< 65$ ,  $\geq 65$  years)
- Gender (Male, Female)
- Diabetes mellitus (yes, no)
- Chronic kidney disease (yes, no)
- CAD presentation (Stable, Unstable)
- HP infection status at enrollment (positive, negative)
- Antiplatelet treatment status at enrollment ( $>6$  months,  $\leq 6$  month)

**Censoring:** Subjects not experiencing any endpoint will be censored at time of death, last contact date (for subjects who withdraw consent or are lost to follow-up) or 180-day  $\pm$  14 days after randomization, whichever comes first.

**Primary Efficacy Analysis:** The primary endpoint analysis will be conducted according to the intention-to-treat (ITT) principle. The main aim of this study is to determine whether the strategy of 6-month DAPT plus 6-month single antiplatelet therapy is superior to 12-month DAPT in terms of the primary endpoint (gastrointestinal injury) after contemporary DES implantation. The null hypothesis ( $H_0$ ) for this analysis is that the incidence of primary endpoint in the experimental group is same as that of the control group, namely  $P_0=P_1$ . The alternative hypothesis ( $H_1$ ) is that the incidences of primary endpoints in the two groups was not equal, namely  $P_0 \neq P_1$ , and the superiority test is conducted at the 2-sided significance level of 0.05. This analysis will be repeated in the Per-protocol (PP) population to support the main results.

The primary and secondary endpoints will be also analyzed in the following clinically

relevant pre-specified subgroups (Part 12.2). Formal interaction testing will be performed using the subgroup  $\times$  treatment allocation as an additional term in the logistic models.

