#### **Ordinal variables include:**

- Gastrointestinal symptoms (pain, nausea/vomiting, dysphagia, other) during the 12 months after enrolment (Protocol Appendix 3).

Ordinal outcomes will be compared between groups using proportional odds logistic regression models. Logistic regression model results will be reported as odds ratios for monotherapy group vs. DAPT group, with 95% CIs and p-values.

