### 9.3.2 Analysis for time-to-event endpoints

Kaplan-Meier curves will be plotted by treatment group. Patients not experiencing a endpoint event during corresponding time interval will be censored at the time of death, last contact date (for subjects withdrawing consent or lost to follow-up) or 365 days, whichever comes first.

A hazard ratio (HR) and two-sided 95% CI for the primary endpoint will be generated using the Cox proportional hazards model. The null hypothesis ( $H_0$ ) for this analysis is that the  $HR = 1$ . The two-sided alternative hypothesis ( $H_A$ ) is that the  $HR \neq 1$ . A test of superiority at the two-sided 0.05 level will be performed using a p-value from a log-rank test.

- All bleeding (BARC types 1–5) during the 12 months after enrollment;
- The incidence of target lesion failure (TLF); cardiac death, target-vessel MI, or clinically-driven target lesion revascularization), during the 12 months after enrollment;
- The incidence of net adverse clinical events (NACE, defined as TLF or BARC type 2–5 bleeding) during the 12 months after enrollment;
- The incidence of stent thrombosis (ARC definite, probable, or definite/probable) during the 12 months after enrollment.

In addition, all secondary endpoints will also be compared across the 3 groups, and for all single group versus group comparisons (12-month DAPT vs 6-month DAPT plus 6-month aspirin monotherapy; 12-month DAPT vs 6-month DAPT plus 6-month clopidogrel monotherapy; and 6-month DAPT plus 6-month aspirin monotherapy versus 6-month DAPT plus 6-month clopidogrel monotherapy).

All analysis will be repeated in the PPS to support the primary results.

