## **9.6 Subgroup analysis**

The primary and secondary endpoints will be summarised in clinically relevant subgroups of the FAS as a whole and by treatment group. For each subgrouping variable, ORs and two-sided 95% CI will be calculated within each subgroup using a Logistic regression with treatment as fixed effect factors. Formal interaction testing on the ratio scale will be performed using the subgroup  $\times$  treatment allocation as an additional term in the Logistic model.

The following subgrouping variables will be considered:

- Age (<65 years,  $\geq$ 65 years)
- Sex (male, female)
- Diabetes mellitus (yes, no)
- Chronic kidney disease (eGFR<60,  $\geq$ 60 mL/min/1.73m^2)
- Acute coronary syndrome (yes, no)

- Prior history of gastrointestinal bleeding (<24 months, ≥24 month)
- HP infection status (yes, no)
- DAPT duration prior to randomization (>6 months, ≤6 months)

Another subgroup analysis will be performed in patients in whom follow-up was complete vs incomplete or otherwise affected by the COVID-19 pandemic (6-month visit after randomization date: before 2020/1/23, after 2020/1/23).

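### The subgroup rule names only logistic models and odds ratios, although four secondary endpoints are analysed overall by Cox regression with censoring

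*Supplement*

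**What the plan says.** SAP section 9.6 sets the scope: "The primary and secondary endpoints will be summarised in clinically relevant subgroups of the FAS as a whole and by treatment group". It then states a single method of estimation: "ORs and two-sided 95% CI will be calculated within each subgroup using a Logistic regression with treatment as fixed effect factors". Interaction is tested with subgroup × "treatment allocation as an additional term in the Logistic model". Protocol v1.4 section 12.2 gives the same scope more briefly and tests interaction with subgroup by "treatment allocation as an additional term in the logistic models", without listing the terms of those models.

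The main analyses differ by type of endpoint:

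- **Primary endpoint and binary secondary endpoints** (SAP 9.2 and 9.3.1): logistic regression.
- **Symptom score** (SAP 9.3.1): "Ordinal outcomes will be compared between groups using proportional odds logistic regression models".
- **BARC bleeding, target lesion failure, NACE and stent thrombosis** (SAP 9.3.2): Kaplan-Meier curves, a log-rank test, and a hazard ratio that "will be generated using the Cox proportional hazards model". Patients without an event are censored at death, last contact or 365 days. The hazard-ratio sentence refers to the primary endpoint, but the section heading and the list beneath it assign the method to these four endpoints.

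Nothing in section 9.6 exempts the four time-to-event endpoints.

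**The concern.** SAP section 6.1 includes patients who withdraw or are lost up to the date they leave the study. Cox regression uses that partial follow-up. A plain logistic model cannot: a patient who leaves at two months without an event must be counted as event-free for the whole period or dropped. If losses differ between arms, the first option biases the odds ratio.

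There is also a reporting problem. A forest plot for NACE, for example, would show subgroup odds ratios beneath an overall hazard ratio. The reader could not tell whether a difference reflects effect modification, the change of scale or the handling of censoring.

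A smaller matter of clarity belongs with this. Neither document lists the terms of the interaction model, and one reading that the wording allows would have a false-positive rate well above 5%.

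**Working it through.** **1. Scope.** SAP 4.1 and 4.2 give 1 primary and 10 secondary endpoints. SAP sections 7 and 9.6 list 8 subgrouping variables plus the COVID-19 split, so 9. Four endpoints have a Cox main analysis: 4 × 9 = 36 of 11 × 9 = 99 subgroup analyses. This counts each endpoint once, over the 12 months listed in 9.3.2, and is an upper limit: the current protocol lists only seven subgroups, and some strata may be too small to analyse.

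**2. The plan's own figure.** The subgroup rule states no number. The simulations below take their sample size and event rates from SAP section 5, which reproduces. With p₀ = 0.47, p₁ = 0.30, ratio 2:1, two-sided α = 0.05, power 90% and pooled p = (0.47 + 2 × 0.30)/3 = 0.357:

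n₀ = [1.96 √(0.357 × 0.643 × 1.5) + 1.2816 √(0.47 × 0.53 + 0.30 × 0.70/2)]² / 0.17² ≈ 127

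That is 381 in total against the stated 384. Power at 128 and 256 is 90.3%, and 384/0.80 = 480 randomized.

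**3. Change of scale alone.** Under proportional hazards with complete follow-up, p₁ = 1 − (1 − p₀)^HR. For an assumed HR of 0.70:

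| DAPT 12-month risk p₀ (assumed) | p₁ | OR |
|---|---|---|
| 5% | 3.5% | 0.69 |
| 20% | 14.5% | 0.68 |
| 40% | 30.1% | 0.64 |

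**4. Censoring added.** The documents give neither event rates for these endpoints nor dropout by arm, so both are assumed. Simulation: N = 480 (160 DAPT, 320 monotherapy), no subgroup, constant hazards, true HR 0.70, dropout independent of events, patients lost without an event coded as no event, 2,000 trials per row. The rate ratio (events over person-time) stands in for the Cox estimate; under constant hazards the two target the same quantity. Entries are geometric means.

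| DAPT risk | Dropout DAPT / monotherapy | OR | Rate ratio |
|---|---|---|---|
| 5% | 1% / 1% | 0.72 | 0.72 |
| 5% | 20% / 20% | 0.71 | 0.71 |
| 5% | 10% / 25% | 0.64 | 0.71 |
| 20% | 1% / 1% | 0.68 | 0.71 |
| 20% | 20% / 20% | 0.68 | 0.70 |
| 20% | 10% / 25% | 0.61 | 0.70 |
| 40% | 1% / 1% | 0.65 | 0.70 |
| 40% | 20% / 20% | 0.66 | 0.70 |
| 40% | 10% / 25% | 0.58 | 0.70 |

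With equal dropout the two agree closely at 5% risk and drift apart by up to about 0.05 at 40%. With unequal dropout the odds ratio overstates the benefit at every event rate, while the rate ratio stays near 0.70.

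**5. Term list of the interaction model.** Simulation for the primary endpoint: 128 DAPT and 256 monotherapy, 47% and 30%, no true interaction, 4,000 trials per cell. The subgroup factor's prognostic OR and its prevalence (30% and 50%) are assumed. Entries are rejection rates at 5%, for 30% / 50% prevalence.

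| Model | Prognostic OR 1 | OR 1.5 | OR 2 |
|---|---|---|---|
| Treatment + product, DAPT as reference | 4.9% / 4.7% | 29% / 31% | 66% / 71% |
| Treatment + product, monotherapy as reference | 5.0% / 4.8% | 18% / 21% | 44% / 49% |
| Treatment + class-coded product, 2-df test | 5.0% / 4.5% | 32% / 37% | 78% / 82% |
| Treatment + subgroup + product | 5.0% / 5.2% | 5.5% / 5.0% | 5.6% / 4.4% |

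Without the subgroup main effect, the product term picks up prognosis. With it, the test holds its level.

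**The case against.** **Small in practice.** The population is low-risk (GRACE below 140), so target lesion failure and stent thrombosis should be uncommon, and at 5% risk with equal dropout the odds ratio and rate ratio coincide to two decimals. Follow-up is fixed at 12 months, and the double blind makes a large difference in dropout less likely. SAP section 11 already plans binary frequencies beside Kaplan-Meier estimates for these four endpoints. All of this stands and limits the size of the point. It does not remove the mismatch: section 9.6 specifies odds ratios as the subgroup result, not as a supplement to hazard ratios.

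**The rule may be meant only for endpoints that have a logistic model.** The protocol's plural allows this. But both rules cover all secondary endpoints, so the four would then have no stated subgroup method, and the wording would still need changing.

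**Two stronger readings that the documents do not support.** A reader might infer that the ordinal symptom score is forced into a binary model. The word binary appears in neither subgroup rule, and the score's own model is a proportional odds logistic regression reporting odds ratios, which the rule's wording can cover. A reader might also infer that the subgroup main effect is left out, so that the interaction tests are invalid. The phrase "using a Logistic regression with treatment as fixed effect factors" describes the models fitted within each subgroup, where the factor is constant and has no main effect to fit. No term list is given for the interaction model, and the usual reading includes both main effects.

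**Conclusion.** The point holds for the four time-to-event endpoints. As written, up to 36 subgroup analyses would ignore censoring and report a measure that cannot be compared with the overall hazard ratio. How far the estimates would move depends on figures the documents do not give. On an assumed true hazard ratio of 0.70, equal dropout leaves the odds ratio at 0.65–0.72 against a rate ratio of 0.70–0.72; dropout of 10% against 25% takes it to about 0.58–0.64.

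The interaction model is under-specified, which is not a demonstrated error. A literal treatment-plus-product fit would give about 18–37% false interactions for a factor with an assumed prognostic OR of 1.5, against about 5% with the main effect included. Those higher rates apply only if the model is fitted that way.

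These are supportive analyses. The primary test, the sample size and the overall secondary analyses are unaffected.

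**What to change.** In SAP section 9.6 and Protocol section 12.2:

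1. State that subgroup and interaction analyses use each endpoint's main-analysis model: logistic regression for binary endpoints; Cox regression with hazard ratios and the censoring rule of SAP 9.3.2 for BARC bleeding, target lesion failure, NACE and stent thrombosis; and proportional odds, confirmed explicitly, for the symptom score. If MACCE is examined in subgroups, it should follow its own method too, which SAP 9.4 takes from 9.3.2.
2. State that every interaction model contains treatment, the subgroup main effect and their product, and that the interaction p-value is for the product term in that model.

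The cost is a few sentences in the two documents and a few lines of code. No further data or patients are needed.
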